### Data analysis

#### Calculation of the statistical power; establishing the sample size; safety

The sample size was established by means of a prior pilot scheme based on a phase II effectiveness trial, with 10 patients monitored over 3 months. There was found to be an improvement of 50% on the baseline YGTSS score (mean total number of tics 12.9 (SD = 11.20) in the experimental group vs. 26.7 (SD = 7.38) in the control group). For the present study, we calculated a mean score of total tics of 13 (SD = 10) after 3 months for the experimental group, and of 23 (SD = 10) for the control group, for a level of significance of 0.05 and a statistical power of 0.8, taking the least favourable case. On the basis of these data, 17 patients per group (34 in total) were needed. This sample size was then over-dimensioned to allow for a possible dropout rate of 10%, and so the minimum sample size was calculated to be n = 38 (19 patients per group).

#### General considerations

A descriptive statistical analysis will be performed, using statistics of central trend and dispersion for the quantitative variables, and frequency distributions for the categorical ones, carried out separately for the experimental and control groups. The baseline variables will be compared using these techniques. A flow diagram will be drawn to show the sequence from the initially eligible population to the one finally included in the study (refusals, dropouts, lost to follow-up, etc.), in accordance with the criteria of the CONSORT guidelines.

A comparison will be made of between-group differences between the initial and final measurements for the diverse elements of the Yale Scale, using unpaired nonparametric tests. For the final within-group comparison, paired nonparametric tests will be used non-parametric Repeat measures with adjustments for baseline imbalances and scores. The same analysis will be performed for the index of psychological well-being, measuring the repercussions of the treatment on family life.

The principal outcome variable (POV) will be taken as the change in the global score on the Yale Scale, adjusted for the baseline values. A simple linear regression model will be made for this POV, and the level of significance set at p < 0.05. Subsequently, a multiple linear regression model will be created, including the variable "Experimental/Control Group", and adjusting for any baseline variables that might be unbalanced. Statistical adjustment was performed by means of a multivariate model including the variable group (experimental and control) and concomitant treatment (Yes/No).

The safety of the treatment will be described in terms of the percentage of adverse events, and according to levels of assignation of responsibility.

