#### Measurement instruments

**The Yale Global Tic Severity Scale**. The Spanish version of the YGTSS will be used. Scoring on this scale ranges from 0 to 100 points. A score of 40 or more on the YGTSS at t0 is defined as a state of exacerbation and therefore a necessary condition for the patient's inclusion in the study.

**PET **will be carried out at the beginning and end of the study in order to detect metabolic changes that may be related to the effectiveness of the treatment. Qualitative changes in the metabolism pattern within the prefrontal cortex and in the basal nuclei will be evaluated. This will be complemented with a quantitative study of the normalized rates of metabolism in such zones.

The Spanish version of the **Psychological General Well-Being Index **will be calculated for the parents, at the beginning and end of the study in order to assess the psychological repercussions of the treatment on family life [30,32]. This scale indicates the subjective feelings and psychological well-being (or otherwise) during the past week.

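### The between-arm comparison of the parents' well-being index is written without baseline adjustment, which is attached instead to a garbled within-group sentence; this costs precision on a secondary aim

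*Protocol article*

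**What the plan says.** Effect on family life is the last of the three secondary goals listed in the Background of the protocol article. It is measured with the PGWBI, which "will be calculated for the parents, at the beginning and end of the study" (Measurement instruments). Evaluations and Study periods agree: one value at t0 and one at day 90 (t4).

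The method is set in Data analysis, General considerations, in this order:

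- Between arms, the comparison is of "between-group differences between the initial and final measurements for the diverse elements of the Yale Scale, using unpaired nonparametric tests". No covariate is named.
- Next: "For the final within-group comparison, paired nonparametric tests will be used non-parametric Repeat measures with adjustments for baseline imbalances and scores".
- Then: "The same analysis will be performed for the index of psychological well-being, measuring the repercussions of the treatment on family life".
- The principal outcome, the change in the global Yale score, is defined afterwards as adjusted for its baseline. The regression models that follow are introduced for that outcome. The PGWBI is not mentioned again.

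**The concern.** The question about family life is answered by comparing the two arms. As written, that comparison uses raw change from t0 to t4 and makes no other use of the t0 score. The adjustment for baseline imbalance appears only in the sentence on the within-group comparison. Imbalance is a difference between arms, so a paired test inside one arm has none to remove.

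Subtracting the baseline is equivalent to adjusting with a slope fixed at 1. When the spread is similar at both visits, the true slope is about ρ, which is below 1, so change scores over-correct. Two things follow: the comparison is noisier than the data require, and part of any chance baseline difference passes into the estimated effect. With fewer than 20 families per arm, such differences are to be expected. The Discussion counts this index among three measures that together are to support the judgement of effectiveness, so the loss is worth avoiding.

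**Working it through.** **The plan's own figure.** The only computed sample size is for tics. Its inputs, from the sample-size section, are three-month means of 13 (experimental) and 23 (control), a common SD of 10, alpha 0.05 and 80% power. Taking the test as two-sided, the normal approximation gives 2 × (1.960 + 0.842)² × (10/10)² = 15.7, so 16 per group. The t-test calculation gives 16.7, so 17. This matches "17 patients per group (34 in total) were needed". With 10% dropout, 17/0.9 = 18.9, so 19 per group and 38 in total, as stated. No calculation is given for the PGWBI, so I use 17 per arm.

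**Assumptions.** SD equal at t0 and t4 (set to 1). The correlation ρ is not in the document; I take 0.3 to 0.7 and also show 0.9.

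**Precision.** Per-patient variance of change is 2(1−ρ). Per-patient variance after adjustment for baseline (ANCOVA) is 1−ρ². The ratio is (1−ρ²)/[2(1−ρ)] = (1+ρ)/2.

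| ρ (assumed) | Change | ANCOVA | Ratio | Loss | 17 × ratio |
|---|---|---|---|---|---|
| 0.3 | 1.40 | 0.91 | 0.65 | 35% | 11.1 |
| 0.5 | 1.00 | 0.75 | 0.75 | 25% | 12.8 |
| 0.7 | 0.60 | 0.51 | 0.85 | 15% | 14.5 |
| 0.9 | 0.20 | 0.19 | 0.95 | 5% | 16.2 |

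The last column is the number per arm at which ANCOVA would match 17 per arm analysed by change. These are large-sample ratios. Estimating the slope in small samples trims the gain a little: simulated ratios at ρ = 0.3, 0.5 and 0.7 were about 0.66–0.67, 0.77–0.78 and 0.87–0.89.

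**Chance imbalance.** The standard error of the baseline difference is √(2/17) = 0.343 SD. Given a baseline difference D, the change contrast is shifted by (1−ρ)D in size. For D of one standard error:

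- ρ = 0.3: 0.7 × 0.343 = 0.24 SD
- ρ = 0.5: 0.5 × 0.343 = 0.17 SD
- ρ = 0.7: 0.3 × 0.343 = 0.10 SD

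**Simulated rejection rates** (normal data, 17 per arm, 6,000 runs; the 0.3 SD row is from a separate run of 4,000). Each cell gives ρ = 0.3 / 0.5 / 0.7.

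| True difference (assumed) | Mann-Whitney on change | ANCOVA | Rank ANCOVA (Quade) |
|---|---|---|---|
| 0 | 0.046 / 0.053 / 0.050 | 0.048 / 0.051 / 0.053 | 0.050 / 0.051 / 0.054 |
| 0.3 SD | 0.11 / 0.14 / 0.18 | 0.13 / 0.18 / 0.21 | not shown |
| 0.8 SD | 0.46 / 0.59 / 0.81 | 0.65 / 0.73 / 0.88 | 0.62 / 0.69 / 0.84 |
| 1.0 SD | 0.64 / 0.79 / 0.94 | 0.84 / 0.90 / 0.97 | 0.81 / 0.87 / 0.95 |

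The first row shows that the planned test keeps its error rate. The other rows show that the gain depends on both ρ and the size of the effect.

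**The case against.** **The sentence is damaged.** The within-group sentence runs two fragments together. Since imbalance has meaning only between arms, the second fragment may have been meant as a separate, adjusted between-arm analysis that the PGWBI would inherit. This is a fair reading, so the document does not prove that an unadjusted analysis was intended. But the text does not state that analysis either. With only t0 and t4 available, a baseline-adjusted repeated-measures analysis of the PGWBI reduces to an adjusted comparison at t4, which is what is recommended here. The same edit settles both readings.

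**An article may leave detail to an analysis plan.** True of detail, but here the quantity tested, the type of test and the place of the adjustment are all stated.

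**A nonparametric test of change is legitimate.** It is: valid at 0.05 and unbiased over randomisations. A reader might infer bias or a raised false-positive rate. The simulation does not support that. The imbalance problem is conditional on the allocation obtained, and only the fraction 1−ρ of the baseline difference comes through.

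**The gain may be small.** At 0.3 SD it is about 2 to 4 percentage points of power, and the aim stays underpowered either way. Part of the gap between Mann-Whitney and ANCOVA is rank against parametric, not adjustment. At 0.8 SD and ρ = 0.8, rank ANCOVA gave 0.93 against 0.94 for the planned test, so no gain. All of this stands and limits the point.

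**Two parents per child.** Because the index is calculated for parents in the plural, a reader might infer that two correlated scores per child enter the test as independent. The article does not say that both parents respond or that each score counts separately, and the choice of respondent is something a condensed article commonly leaves to the full protocol. The point is not made here.

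**Conclusion.** The point holds as a matter of efficiency and clarity, not validity. As written, the between-arm PGWBI comparison has no baseline covariate, and the stated adjustment sits where it cannot act on a difference between arms.

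The size of the loss rests on an assumed ρ and on equal SDs at the two visits: substantial at ρ of 0.5 or below, about 5% at 0.9. The power figures also rest on assumed effect sizes that have no source in the document. The direction is clear for ANCOVA whenever ρ is meaningfully below 1; for rank ANCOVA the advantage can vanish at high ρ.

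Only a secondary aim is affected. The principal outcome has its own baseline adjustment, and the sample size reproduces and does not change. The correction is worth making because it uses data already collected.

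**What to change.** In Data analysis, General considerations:

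1. Replace the sentence that gives the PGWBI the same analysis as the Yale elements with an explicit between-arm model: ANCOVA of the day-90 PGWBI on arm with the t0 PGWBI as covariate, reported as the adjusted arm difference with its 95% confidence interval. If the nonparametric approach is to be kept, name a rank ANCOVA (Quade) with the same covariate. The confidence interval for the adjusted difference applies where ANCOVA is used.
2. Remove the baseline-imbalance adjustment from the within-group sentence, leaving the paired test as a description of change inside each arm. If a separate adjusted between-arm analysis was meant, say so in its own sentence.

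The cost is two sentences. It needs no new data, visits or patients, and adds no burden for families. The article reports the study as in progress, so the change should be made before treatment codes are opened.

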## Discussion

TS is considered to be a rare neurological illness, although increasingly high rates of prevalence are being reported in current studies. The condition is seldom diagnosed, due to ignorance of its existence and characteristics [7]. Until very recently, TS was only recognized as such for the most severe cases, in which there was an important degree of functional limitation and very evident coprolalia. Although this situation is changing, TS is still considered an uncommon disease.

Few clinical studies have been made with children, because, in addition to the normal difficulties arising in this kind of study (with adults), legal considerations must be borne in mind, due to the logical necessity to protect minors. Nevertheless, such studies are clearly needed [33].

TS is a neurological illness, and its physiopathological and inherited alterations, as well as aggravating environmental factors, are increasingly well understood [10]. Effective treatment is provided by dopamine post-synaptic D2 receptor-inhibiting neuroleptic agents [34,35]. Other types of medication, such as anti-epileptic drugs, have also been applied, although the evidence of their effectiveness is less apparent [36,37]. However, the control of TS symptoms provided by the latter kind of treatment is only partial, and side effects such as sedation and dysphoria are common, as are others that are potentially very serious (tardive dyskinesia, arrhythmia or sudden death) [20,38,39]. In view of these considerations, many other forms of treatment have been studied, of varying nature and effectiveness; these include drugs that act on the central nervous system, botulinum toxin, acupuncture, plasmapheresis, conventional neurosurgery and, more recently, deep brain stimulation [40-45]. This diversity suggests that the illness is, as yet, poorly controlled, especially in the most severe cases.

The possibility of a complementary treatment with magnesium and vitamin B_6 _would represent an important improvement in controlling the illness, by reducing the need for neuroleptic drugs and other medication; it would also reduce the amount and severity of side effects.

The alternative therapy proposed in this paper is based on theoretical principles, but also on specific communications and on a prior study, on which the present protocol is based [27].

In clinical terms, magnesium deficiency is related to neuromuscular hyperexcitability, and may give rise to convulsions, chorea and athetoid movements. It has also been related to biochemical and genetic alterations that may provoke the symptoms evidenced by children with TS [46].

The enzyme kynureninase requires the presence of both magnesium and pyridoxal phosphate, and so in cases of hypomagnesemia there are high levels of kynurenines in the blood – which is the case with TS. Abnormally high levels of kynurenines provoke anxiety, an increased release of noradrenaline, locomotory hyperactivity, tics, increases in quinolinic acid, heightened sexual activity among females, reduced levels of serotonin and blocking of the GABA receptors. Therefore, this enzyme has been related to the presence of tics, anxiety and coprolalia-copropraxia [47].

A deficit of magnesium reduces the activity of vitamin B_6_, by inhibiting the activity of the alkaline phosphatase required to achieve its active form in the tissues, pyridoxal phosphate. A deficit of vitamin B_6 _activity has been related with raised levels of kynurenines, spasmodic movements, abnormal movements of the head, hyperirritability, increased sympathetic stimulation and heightened sensitivity to glucocorticoids. The symptoms worsen in situations of stress and with the administration of catecolamines and glucocorticoids [48].

Magnesium deficit increases NMDA receptor activity, producing greater neural excitability. In consequence, there is heightened anxiety and orofacial tardive dyskinesia, an increased release of dopamine, more defensive behaviour and greater modulation of serotonin receptors. Furthermore, other symptoms may be affected, such as migraine, which is more frequent among patients with TS [49].

This situation also raises the levels of substance P, and is associated with defensive behaviour, heightened response to stress and to allergenic phenomena.

It should be noted, however, that to date no clinical trials have been published corroborating this hypothesis [50]. In view of the fact that current treatment with neuroleptic medication only achieves partial effectiveness and may cause severe side effects, we believe there is reason to carry out clinical trials with the proposed, less aggressive, substances [38].

The composition of multivitamin and mineral compounds is very diverse, but from a theoretical standpoint, taking into account their pharmacological properties and following the hypothesis set out above, we consider that clinical trials should be focused firstly on the administration of magnesium and vitamin B_6_. Both substances present a wide therapeutic margin and have very few side effects; moreover, they are authorized for similar indications among children and have a long history of therapeutic use.

Magnesium ions are fundamentally intracellular or located in the bones, with only 1% being extracellular; in consequence, magnesium levels in plasma do not accurately reflect the content in the body. Traditionally, it has been used intravenously to treat severe nutritional deficit, as an antiarrhythmic agent and in cases of eclampsia-preeclampsia. Orally-administered magnesium has been used as a nutritional supplement. It can be given to children. It is contraindicated in cases of acute or chronic decompensated renal insufficiency, myasthenia gravis, diabetic coma and Cushing's disease. The recommended physiological dose is 0.2–0.5 mEq/kg/day [51].

Vitamin B_6 _(pyroxidine) is a hydrosoluble vitamin with a wide therapeutic margin. In clinical and pharmacological trials, it has been shown to have interesting properties, participating in oxidative deamination, transamination and decarboxylation; it also participates in the decarboxylation of glutamic acid to GABA, from DOPA to dopamine and from 5-hydroxytrytophan to seratonin. It presents anti-convulsant properties and seems to exercise a neuroprotective and antitoxic effect. It can be administered to children, and has been authorized for use to treat children with alterations in character, language and behaviour; learning difficulties; delayed learning to walk; convulsive illnesses; intoxication of the central nervous system; trembling; and Parkinson's disease. The dosage provided may vary widely, as renal elimination ensures its toxicity is minimal [52].

As the activity of magnesium is a consequence of its ion fraction, it is mainly intracellular and bears little correlation with the magnesium in serum. We do not believe clinical conclusions can be drawn from the measuring of magnesium levels in serum [53]. In the same way, determining the levels of vitamin B_6 _in serum would not be useful, in view of the fact that the problem lies in the activity deficit [48].

The statistical parameters to be used in this protocol are derived from the above-mentioned prior study carried out by our research group; this was a phase II clinical trials of the effectiveness and safety of the treatment in question. It was useful for pre-determining the degree of improvement that could be expected among the experimental group and, therefore, the minimum sample size needed, together with the mean and standard deviation values measured on the YGTSS.

This prior study showed that the treatment produced a significant decrease in the YGTSS score, with no side effects. Nevertheless, this was a pilot study, with methodological limitations that we seek to overcome in the present protocol [54].

In turn, the methodological instrument that will be used was also developed in a previous study of ours, namely the YGTSS translated into Spanish, adapted and validated for the local population [31].

The population chosen for this study is deliberately restricted, being limited to children aged 7–14 years, which is the age group in which clinical exacerbation, in theory, is greatest. By this limitation, we seek to obtain a population group of very homogeneous characteristics and, at the same time, one presenting severe symptoms, defined as a high score on the YGTSS (≥40).

It may be difficult to recruit the necessary numbers of patients for the sample size envisaged, given the nature of the clinical condition, the relative rarity of its diagnosis and the fact that children are involved. We hope to overcome this difficulty by expanding the geographic scope of the study and the number of medical personnel involved in recruiting suitable patients.

The follow-up period of three months is based on the natural course of the illness, with exacerbations and remissions lasting approximately this length of time. We believe that if the patient enters the study at the onset of a period of exacerbation, the YGTSS score will be high and it will be easier to identify significant differences, with the symptoms being controlled to a greater extent, and more quickly, among the experimental group than among the control group.

The reason for performing a PET on the experimental group before and after the administration of the medication is to objectify the dopaminergic activity within the basal nuclei and in the prefrontal cortex, as well as to reveal any alterations occurring in these areas as a result of the medication administered. However, these images are of low specificity and might not enable clear-cut conclusions to be drawn. Nevertheless, it seems reasonable to attempt to support the results of the clinical evaluation with these alternative, objective data. Be that as it may, these images will be of use as a basis for subsequent studies [15,16].

It is also important to assess the repercussions on family life (which tends to be greatly impaired in severe cases) of an improvement in the control of TS symptoms among children. The PGWBI reflects psychological well-being (or otherwise); it is based on theories of evaluation of the domestic environment and is an appropriate means of determining the distortion produced by TS within the household [30,32]. We have no doubt that a direct correlation will be found between the children's symptoms and the psychological well-being within the family home.

The joint application of these three measurement methods, namely the objectification of tics and incapacity, the assessment of metabolic changes in the circuits of the basal ganglia and of the cortex, and the evaluation of stress within the family, will enable us to reach an objective judgement as to the effectiveness of the treatment being tested.

In summary, treatment for TS continues to present important shortcomings and further clinical trials are necessary in this respect, especially among children.

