**Methodology:**

Randomized, blinded clinical trials. Phase IV study (new proposal for treatment with magnesium and vitamin B_6_). Scope: children in the geographic area of the study group. Recruitment of subjects: to include patients diagnosed with TS, in accordance with DSM-IV criteria (307.23), during a period of exacerbation, and provided none of the exclusion criteria are met. Instrumentation: clinical data and the YGTSS score will be obtained at the outset of a period of exacerbation (t0). The examinations will be made after 15 (t1), 30 (t2), 60 (t3) and 90 days (t4). PET will be performed at the t0 and t4. We evaluated decrease in the overall score (t0, t1, t2, t3, t4), PET variations, and impact made by the treatment on the patient's life (Psychological General Well-Being Index).

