We have designed a clinical trials to evaluate the effects of magnesium and vitamin B_6 _supplements on the clinical condition of children with TS. This supplementation is authorized for children and already commercially available; therefore, our aim in the present study is to confirm a possible new indication. The study should include children up to the age of 14 years, diagnosed with TS; this age limit was chosen as it is then when a standstill or remission of the symptoms may occur. The minimum duration of treatment and follow-up for these children should be three months, in view of the natural evolution of the illness, with spontaneous remissions and exacerbations. The symptoms most easily measured are the presence and severity of tics.

We present a new therapeutic approach to TS, based on the hypothesis that a deficit of vitamins or oligoelements, or a reduction of their activity, aggravates this pathology and often provokes severe comorbidity. Moreover, we take into account that current treatment protocols are frequently ineffective among many children and present important potential side effects.

Thus, we propose the following:

Main goal – to show that, with respect to placebo treatment, the combination of 0.5 mEq/Kg magnesium and 2 mg/Kg vitamin B_6 _reduces motor and phonic tics and incapacity in cases of exacerbated TS among children aged 7–14 years.

Secondary goals – to assess the safety of the treatment, in terms of adverse events; to describe metabolic changes resulting from the treatment, as revealed by PET; and to measure the impact of this treatment on the quality of family life.

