## Methods and design

### Design

#### Type of clinical trials

Blind, randomized clinical study, Phase IV (new indication for supplementary magnesium and vitamin B_6_).

This study began in October 2007 and is currently in progress.

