#### Instrumentation

The clinical data and the YGTSS score at the onset of the period of exacerbation of the clinical condition (t0) will be noted. The parents/guardians will be informed, and on receipt of their informed consent, the previously randomized medication will be provided. This medication is to be taken at the patient's home, and follow-up will be performed, at the healthcare clinic, at 15(t1), 30(t2), 60(t3) and 90(t4) days. PET will be performed at the start and end of the experimental period, for 15 patients. The psychological impact of the treatment on the families concerned will be measured using the Psychological General Well-Being Index (PGWBI) [30].

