#### Study periods

t0 Entry into the study

   When the child's parents/guardians consider a period of exacerbation is beginning, they enter the active phase of the study. The YGTSS score is assessed, taking into account that a score of at least 40 is a prerequisite for entry into the study.

   The baseline PET is carried out for patients included in the study.

   The PGWBI for the parents/guardians is calculated.

**t1 At 15 days**.

   The YGTSS is calculated.

t2 At 30 days

   The YGTSS is calculated.

t3 At 60 days

   The YGTSS is calculated.

**t4 At 90 days. End of study period**.

   The YGTSS is calculated.

   PET control.

   PGWBI for parents/guardians.

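### The PET population is stated inconsistently (15 patients, patients included in the study, the experimental group); the experimental-group wording, if followed, leaves no control scans and can make a scan a sign of allocation

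*Protocol article*

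**What the plan says.** The protocol article describes PET in several places.

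- Instrumentation: "PET will be performed at the start and end of the experimental period, for 15 patients". No arm is named.
- Study periods, at t0: "The baseline PET is carried out for patients included in the study". A control PET is listed at t4, and no subset is mentioned.
- Abstract, Methodology: "PET will be performed at the t0 and t4". Measurement instruments says that the scan "will be carried out at the beginning and end of the study in order to detect metabolic changes that may be related to the effectiveness". Neither mentions a subset or an arm.
- Discussion: "The reason for performing a PET on the experimental group before and after the administration of the medication" is to document activity in the basal nuclei and prefrontal cortex and any alteration that the medication causes.

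The secondary goal in Background to the study is "to describe metabolic changes resulting from the treatment, as revealed by PET". The closing part of the Discussion lists PET with the tic scale and the family measure as the three methods that together will support a judgement on effectiveness. The design is given as "Blind, randomized clinical study, Phase IV", with a placebo made to match the active product in excipients and volume. The planned sample is 38, 19 per group.

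**The concern.** The statements do not define one scanned population, and the Discussion is the only place that names an arm. A site that follows it would scan treated children only. Two consequences follow from that reading.

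First, PET would have no comparator. Children enter at the onset of an exacerbation, and the Discussion says that exacerbations and remissions last about as long as the three-month follow-up. A before-after change in treated children would mix drug effect with natural remission, yet both the stated goal and the Discussion attribute PET change to the treatment.

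Second, scanning by arm ties a visible procedure at t0 to allocation. The YGTSS is scored from a semi-structured interview, generally with the parents, who know whether their child was scanned. The t1 to t4 ratings all come after the baseline scan. A leak of allocation would therefore reach the primary outcome as well as the PET aim.

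**Working it through.** **Planned sample.** Inputs from the sample-size section: means 13 and 23, SD 10, significance level 0.05, power 0.8, dropout 10%. The standardised difference is (23 − 13)/10 = 1.0. A two-sided two-sample t-test needs 16.7, so 17 per group, or 34. Allowing for dropout, 34/0.9 = 37.8, so 38 (19 per group). The plan's figure reproduces and the PET question does not affect it. No sample-size calculation is given for PET.

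**Who is scanned, at two scans per child.**

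| Source | Reading | Children | Scans |
|---|---|---|---|
| Instrumentation | 15 patients, arm not named | 15 | 2 × 15 = 30 |
| Study periods | patients included, no subset | 38 | 2 × 38 = 76 |
| Discussion | experimental group | 19 | 2 × 19 = 38 |

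The first and third can be joined as 15 of the 19 experimental children. The article does not say this, and it still does not fit Study periods.

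**What a scan would reveal if only the experimental arm is scanned.** This assumes that the observer knows the rule.

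- All 19 scanned: scan status identifies 38 of 38 allocations.
- 15 of 19 scanned: all 15 scanned children are on active treatment. The unscanned number 38 − 15 = 23, of whom 19 are on placebo: 19/23 = 83%. Guessing active for the scanned and placebo for the rest is right for (15 + 19)/38 = 34/38 = 89%, against 50% with an intact blind.
- Control scans: 0 in either case.

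**What the missing control could do.** The documents give no PET variance, so the size of natural change is an assumption. Let remission alone shift PET by d standard deviations of the within-child change, with no drug effect. A two-sided 5% paired t-test in 15 treated children has 14 degrees of freedom, critical value 2.145 and noncentrality d × √15.

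| Assumed d | Noncentrality | Probability of a significant change with no drug effect |
|---|---|---|
| 0.2 | 0.77 | 11% |
| 0.5 | 1.94 | 44% |
| 0.8 | 3.10 | 82% |

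The article specifies no PET test. The table only illustrates how easily an uncontrolled change could be read as a treatment effect.

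**The case against.** The strongest reply is that the operative text contains no restriction to one arm. Instrumentation, Evaluations, Measurement instruments, Study periods and the abstract are all neutral on arm; only a sentence of rationale in the Discussion is not. A specific figure normally governs a general visit list, and Study periods does not say that every included patient is scanned, so 15 may simply be the rule. On that reading there is no threat to the blind. This largely stands as regards severity. It does not remove the inconsistency, because the 15 have no stated arm and the one place that names an arm names the experimental group.

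A reader might infer that the blind is actually broken. The documents do not support that. It would require the Discussion wording to be followed, and families or raters to know what a scan implies. The article does not say what they are told, and the allocation envelopes are kept in the pharmacy.

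It is also fair to say that PET is a secondary aim, worded as description, and that the Discussion concedes the images are not very specific and may prove inconclusive. That stands, but the same section then counts PET among the three methods for judging effectiveness.

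The Discussion speaks of dopaminergic activity, while Measurement instruments specifies metabolism ("Qualitative changes in the metabolism pattern within the prefrontal cortex and in the basal nuclei will be evaluated"). A reader might take this as a second contradiction of equal weight. It is a separate, minor matter of wording: the goals and methods refer consistently to metabolism.

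**Conclusion.** The point holds as an internal inconsistency with a conditional consequence. That the PET population is not consistently defined is plain from the text. The figures 38 and 19 are the planned sample and arm size applied to wording that gives no number.

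If the experimental-group wording is followed, the absence of control scans is certain, and PET change then cannot be attributed to treatment. The possible loss of blinding, up to 89% or 100% of allocations guessable, also depends on people knowing the scanning rule. It is a risk, not a demonstrated breach. The 11% to 82% range rests on assumed values of natural PET change.

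This should be fixed, but it does not by itself undermine the trial: the unblinding is conditional and PET is a secondary descriptive aim.

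**What to change.** State one rule and use it in Instrumentation, Study periods and the Discussion:

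- PET at t0 and t4 in 15 patients, the number already given;
- the 15 selected independently of allocation, with both arms eligible;
- the phrase limiting PET to the experimental group deleted from the Discussion;
- the t0 to t4 change described by arm.

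The trial began in October 2007 and is in progress. If children already enrolled were scanned according to arm, report this, and limit the PET conclusion for them to an uncontrolled description that is not attributed to treatment.

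Cost: if scanning is already neutral on arm, this is a change of wording and the total stays at 30 scans. If current practice is experimental-arm only, some scans will fall in placebo children and fewer treated children will be imaged.
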